### Eligibility Criteria

All students (N=1300; 88% female and 12% male) enrolled in programs at the Bachelor of Science and Master of Science levels as well as all academic and nonacademic employees of BFH-DHP are eligible and will be invited to participate in this comprehensive, web-based survey. BFH-DHP runs these educational programs in the fields of nursing, nutrition and dietetics, midwifery, and physiotherapy. Individuals that are not employed or enrolled at the university will not be eligible for this study.

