#### Statistical Analyses

Parametric and nonparametric statistics will be used to report results from both surveys and to compare survey results with reference values obtained from the general population during pre–COVID-19 conditions. For descriptive analyses, central tendencies will be expressed as means or medians, and variation will be expressed as SD and 95% CI or interquartile ranges (25th and 75th percentiles), respectively. Kruskal-Wallis tests with posthoc Bonferroni corrections will be used to assess differences between independent groups. Results will be presented as frequency tables or as figures with boxplots.

For the explorative correlation analysis, health profession divisions, students’ academic level, and employee status will be recoded as follows: nutrition and dietetics = 1, midwifery = 2, nursing = 3, physiotherapy = 4, BSc = 1, MSc = 2, and employee = 3. The Spearman rank order correlation coefficient will be used to assess associations between the different variables under analysis. Results will be presented in a correlation matrix.

Statistical analyses will be conducted using SPSS software (version 26.0; IBM Corp.). Statistical significance will be set at the 5% level of error.

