## Results

This longitudinal study was started during the lockdown in Switzerland, in mid-April 2020 and will be completed in May 2021. The first phase of the study is underway, and data from 823 participants will be evaluated.

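### Division and student/employee status are nominal but are numbered and entered in a Spearman matrix, so those cells depend on an arbitrary label order

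*Protocol article*

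**What the plan says.** All of the relevant text is current and stands in the Statistical Analyses section of the protocol article, except where noted.

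- Purpose of the codes: "For the explorative correlation analysis, health profession divisions, students’ academic level, and employee status will be recoded as follows".
- Division: "nutrition and dietetics = 1, midwifery = 2, nursing = 3, physiotherapy = 4".
- Academic level and employee status, on one scale: "BSc = 1, MSc = 2, and employee = 3".
- Method: "The Spearman rank order correlation coefficient will be used to assess associations between the different variables under analysis". Presentation: "Results will be presented in a correlation matrix".
- Error level, stated generally and without exempting this matrix: "Statistical significance will be set at the 5% level of error".
- Who the employees are (Eligibility Criteria): "all academic and nonacademic employees of BFH-DHP are eligible".
- Respondents to the first survey (Results): "data from 823 participants will be evaluated".

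The Data Management section places the correlations second, after each lifestyle domain has been analysed separately, and limits them to complete cases. It also plans subgroup comparisons by division, academic level and employee status. The Statistical Analyses section assigns comparisons of independent groups to Kruskal-Wallis tests with Bonferroni-corrected post hoc comparisons. No reason is given for either numbering, and no indicator coding or nominal measure of association is named.

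**The concern.** Spearman's rho measures monotone association, so both variables must have an order. Nutrition and dietetics, midwifery, nursing and physiotherapy have none. Status is a mixed case. BSc can be placed below MSc, but the third code pools academic and nonacademic staff, who do not form a level above MSc. One code out of order is enough to make the three-code variable nominal.

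The codes have no other stated use, so they are not mere database labels. Every matrix cell that pairs division or status with an outcome, or the two with each other, would show a number that another equally defensible numbering would change. A reader could take a coefficient near 0 as evidence that the divisions are alike, or a positive one as a gradient across professions. The statistic supports neither reading.

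**Working it through.** The protocol gives no correlation, group size or effect on this point, so there is no figure to reproduce. The check shows how rho depends on the numbering, under assumed values.

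**Inputs.** N = 823 (Results), an upper bound because this step uses complete cases only. Two-sided 5% level (the protocol does not state sidedness). Group sizes and shifts are assumptions.

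**Formula.** Rho is the Pearson correlation of the ranks. For four equal groups, let s = code - 2.5 and let m be a group's mean fractional rank minus 0.5. Then

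rho = [sum of s × m over the four groups / 4] / (SD of codes × SD of fractional ranks)

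with SD of codes = √1.25 = 1.118 and SD of fractional ranks = 1/√12 = 0.2887. The product is 0.3227.

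**Pattern A: the divisions coded 2 and 3 are higher by 0.3 SD, normal outcome.**
- The chance that a member of a higher division exceeds a member of a lower one is Φ(0.3/√2) = 0.584. So m = +0.042 in the two higher divisions and -0.042 in the others (0.5 × 0.084).
- Protocol numbering: (-1.5)(-0.042) + (-0.5)(0.042) + (0.5)(0.042) + (1.5)(-0.042) = 0, so rho = 0.
- Higher divisions numbered 3 and 4: the sum is 4 × 0.042, so rho = 0.042/0.3227 = 0.130. Reversing the numbering gives -0.130.
- Kruskal-Wallis, same for every numbering: H ≈ 12 × (0.042 × 823)²/824 ≈ 17.4.

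Direct calculation agrees: H = 17.34, p = 0.0006; rho = 0.000 (p = 0.99) in protocol order; range -0.130 to +0.130; 8 of 24 numberings beyond the critical value 1.96/√822 = 0.068.

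**Other assumed patterns for division (direct calculation; shifts in SD units).**

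| Group sizes | Shifts | Kruskal-Wallis p | rho, protocol order | Range over 24 | Significant |
|---|---|---|---|---|---|
| equal | 0/0.5/0.5/0 | 3.4e-10 | 0.001 (p = 0.99) | -0.214 to +0.214 | 16 |
| equal | 0/0/0/0.5 | 1.1e-07 | 0.160 | -0.160 to +0.160 | 12 |
| 100/120/350/253 | 0/0.3/0.3/0 | 0.00068 | -0.057 (p = 0.10) | -0.131 to +0.131 | 14 |

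**Skewed activity data (simulation).** Equal divisions, log-normal with log-SD 0.9, the two middle-coded divisions higher by 0.4 on the log scale. Kruskal-Wallis was significant in 100% of runs. Under the protocol's numbering mean rho was about 0, significant in 4.5% to 7.5% of runs across repeats of the simulation. Over the 24 numberings the extremes averaged -0.21 and +0.21, and 14 to 15 were significant. The formula gives 0.19 for the best fixed numbering: 0.4/0.9 = 0.444 SD, Φ(0.444/√2) = 0.623, 0.0617/0.3227 = 0.191. The simulated extreme is a little larger because it takes the largest value in each data set.

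If only the division coded 4 is higher by 0.4, m = 0.75 × 0.1233 = 0.0925 there and -0.25 × 0.1233 = -0.0308 elsewhere. Then rho = [(1.5 × 0.0925 + 1.5 × 0.0308)/4]/0.3227 = 0.143. Simulation gave 0.14 to 0.15, significant in 98% to 99% of runs.

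**Status, three codes.**
- Equal groups, shifts 0/0.5/0: H = 41.82, p = 8e-10. The BSc-MSc-employee order gives rho = 0.000 (p = 0.99); other orders reach ±0.195 (p about 2e-8).
- Groups 500/73/250, same shifts: Kruskal-Wallis p = 0.0005. The protocol order gives rho = 0.026 (p = 0.46); other orders reach ±0.078 (p = 0.026).

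**The case against.** The strongest reply is that little rests on these cells. The step is labelled explorative and comes second. Total physical activity, the primary outcome, does not depend on it. Whether outcomes differ by division or status is already put to the Kruskal-Wallis tests, which ignore label order. All of this stands and limits the severity. It does not give the cells a meaning, because an explorative label does not supply an order where there is none.

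Three stronger readings may tempt a reader, and the documents do not support them:

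- **That the matrix will produce excess false positives.** The counts of significant numberings suggest this, but the protocol fixes one numbering in advance and nobody selects among 24. With no group differences, the fixed numbering rejected in about 5% to 6% of simulated runs, in line with the nominal 5%.
- **That the protocol's numbering will hide real differences.** Rho near 0 arises in the symmetric pattern with the two middle codes raised. If only the division coded 4 is higher, the same numbering detects it. The documents give no division sizes or effects, so neither pattern can be called likely.
- **That disagreement with Kruskal-Wallis would itself show an error.** One tests a trend over the codes and the other any difference between groups, so they can differ legitimately. The trouble is that a trend over these codes answers no question.

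**Conclusion.** The concern holds, as a minor to moderate defect. The plan states a rule that yields uninterpretable coefficients for division and for status as coded; it is not a detail left open for an analysis plan. That rho depends on label order follows from its definition and applies whenever groups differ. The particular values (0 under the protocol's numbering against extremes near ±0.21, or about 0.14 to 0.15 in the one-division pattern) rest on assumed group sizes and shifts, and on N = 823 as an upper bound. The cost is lost meaning in these cells and lost power against non-monotone differences. Two things are unaffected: the correlations among activity, diet, alcohol and sleep, and the group comparisons by Kruskal-Wallis. It would be wrong to infer that the study's main results are at risk.

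**What to change.** Remove division and status from the Spearman matrix and delete the numeric recoding that serves it. Keep the matrix for ordinal or continuous variables: total activity, Mediterranean diet score, alcohol units, hours of sleep and sleep quality. Report how outcomes relate to division and status through the Kruskal-Wallis tests already planned, optionally with an effect size such as epsilon-squared. If the association of division with status is wanted, use Cramér's V.

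The cost is a change of wording in the Statistical Analyses section. No new data are needed and the planned tests stay as they are. An adjusted model is not required to cure this defect.

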#### Data Management

Data management will be performed on the BFH-DHP server. The EvaSys system will automatically store data collected from all study participants as comma separated variables (.csv) files. All data files will be imported and merged to a single data file in Excel (2018; Microsoft Corp).

Data cleansing will be performed by one researcher (JT) who will check and solve for example dot-comma decimal signs incompatibilities and to control plausibility of the data (ie, range checks). The iPAQ-SF data-cleansing guidelines will strictly be adhered to, that is, participants with incomplete (missing) data or those who responded “don’t know” will be removed from the analyses.

Data analyses will be carried out in 2 steps. First, data on physical activity, nutritional habits, alcohol consumption, and sleeping habits will be separately analyzed. Second, an explorative correlational analysis will be conducted, including only those participants with a complete set of data for all lifestyle habits under evaluation. Subgroup analyses will be conducted to compare differences in the outcomes between health profession divisions or between students’ academic levels (ie, BSc and MSc) and employee status.

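### The exploratory Spearman matrix pools all divisions and statuses, so its habit-by-habit coefficients cannot separate links within a group from differences between groups (low severity)

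*Protocol article*

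**What the plan says.** Data Management describes a second analysis step: "an explorative correlational analysis will be conducted, including only those participants with a complete set of data for all lifestyle habits under evaluation". Statistical Analyses then fixes three things for it.

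- **Coding of groups:** "health profession divisions, students’ academic level, and employee status will be recoded as follows: nutrition and dietetics = 1, midwifery = 2, nursing = 3, physiotherapy = 4", with BSc, MSc and employee coded 1, 2 and 3.
- **Coefficient:** "The Spearman rank order correlation coefficient will be used to assess associations between the different variables under analysis".
- **Output:** "Results will be presented in a correlation matrix".

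A coefficient between division and a habit can exist only if the divisions are analysed together. Pooling therefore follows from the text, although the article does not use the word. No partial or by-group coefficient is named.

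Group differences are addressed elsewhere. Data Management states: "Subgroup analyses will be conducted to compare differences in the outcomes between health profession divisions or between students’ academic levels", and also by employee status. Statistical Analyses supplies the test: "Kruskal-Wallis tests with posthoc Bonferroni corrections will be used to assess differences between independent groups". The significance level is general: "Statistical significance will be set at the 5% level of error".

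**The concern.** The grouping variable is close to the outcomes. Eligibility Criteria says: "BFH-DHP runs these educational programs in the fields of nursing, nutrition and dietetics, midwifery, and physiotherapy". The diet score is the subject of one of these professions, and physical activity is close to that of another. Division is therefore a plausible source of differences in both habits.

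Two distortions are possible if a pooled coefficient is read as a statement about similar people. If one division is higher on activity and a different one on diet, the pooled coefficient is pulled down, and a real link within divisions can be missed. If the same division is higher on both, a positive coefficient appears with no link within any division.

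The matrix is the only planned analysis of how the habits go together. The Discussion intends the results to inform counselling of students and employees and workplace health promotion, where a reader will naturally ask whether more active people also eat or sleep better.

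**Working it through.** **Inputs from the article.** Spearman coefficient, 5% level (two-sided assumed), four divisions, three statuses, and 823 first-survey participants (Results). Because the matrix uses complete cases only, 823 is an upper limit. The article gives no correlation, power or sample-size figure for this analysis, so there is none to reproduce.

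**Assumptions, not in the article.** Two habits with SD 1 within division; a within-division correlation r of 0.10 or 0; division shares p; mean shifts of d SD.

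**Critical value.** 1.96/√(823 − 1) = 0.068.

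**Scenario A: physiotherapy shifted on activity, nutrition on diet, equal shares.** On the ordinary correlation scale:

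- covariance = r − p₁p₄d² = r − 0.0625d²
- variance of each habit = 1 + p(1 − p)d² = 1 + 0.1875d²
- pooled correlation = (r − 0.0625d²)/(1 + 0.1875d²)

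For r = 0.10 and d = 0.8 this is (0.10 − 0.04)/1.12 = 0.054. Simulation with Spearman ranks at n = 823 agrees:

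| Shift d (SD) | Formula, r = 0.10 | Simulated pooled rho, r = 0.10 | Pooled test significant, r = 0.10 | Pooled test rejects, r = 0 |
|---|---|---|---|---|
| 0.3 | 0.093 | about 0.09 | about 71% | about 5% |
| 0.5 | 0.081 | about 0.08 | about 59% | about 8% |
| 0.8 | 0.054 | about 0.05 | about 30% | about 15% |
| 1.0 | 0.032 | about 0.03 | about 13% | about 31% |

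After ranks are centred within division, the coefficient is about 0.095 at every shift and is significant in about 77% of runs. With r = 0 the centred test rejects in 4% to 6%. Repeated simulations differ by two or three percentage points.

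**Unequal shares (nutrition 15%, midwifery 15%, nursing 45%, physiotherapy 25%).** Scenario A is weaker. At 0.8 SD and r = 0, the pooled correlation is −0.15 × 0.25 × 0.64/√(1.12 × 1.0816) = −0.022, with rejection in about 9%. With r = 0.10 at the same shift, the pooled test is significant in about 48% of runs, against about 78% within division.

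**Scenario B: one division higher on both habits, r = 0.** The pooled correlation is p(1 − p)d²/[1 + p(1 − p)d²]. For a 25% division this is 0.045 at 0.5 SD and 0.107 at 0.8 SD. For a 15% division it is 0.031 and 0.075. Over these shares, pooled rejection is about 12% to 26% at 0.5 SD and 52% to 85% at 0.8 SD.

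**Do the other planned steps separate the two sources?** The Kruskal-Wallis tests compare outcome levels between groups. The coded division and status rows add coefficients of their own. Neither changes the activity-by-diet cell.

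**The case against.** The strongest reply is that nothing here is an error. The analysis is labelled explorative, the primary outcome does not depend on it, and the stated aim concerns students and employees of the whole department. For that population the pooled Spearman coefficient is a valid description. This stands. A reader might infer that the pooled coefficients are false, or that all conclusions should move to an adjusted coefficient. The article does not support that: it claims neither a within-profession nor a causal association. When the within-division correlation is zero but group means differ, the department-wide correlation really is non-zero, so a pooled rejection is a false positive only for the within-group question.

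The size is also uncertain. At shifts of 0.3 SD the effect is slight, and at 0.5 SD in scenario A rejection is only about 8%. Large effects need shifts of about 0.8 SD, and unequal divisions can weaken them. This stands too.

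A reader might also infer that the plan ignores division and status. It does not: both are in the matrix, outcome levels are compared across them, and large group differences would be visible there. But seeing that groups differ does not tell a reader how much of a habit-by-habit coefficient is due to it.

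Finally, a full analysis plan could add by-group coefficients. The point here is narrower: the article does specify the coefficient, the coding and the output, and that specification leaves the two sources mixed.

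**Conclusion.** The point holds at low severity. As specified, the matrix describes how habits go together across the department, but it cannot answer whether they go together among people of the same profession and status. In the scenarios tried, the effect ranges from slight at 0.3 SD to considerable at 0.8 SD and above. Which of these applies is unknown, because the article gives neither group differences nor division shares. The figures also take all 823 respondents as complete cases and vary division only, not status.

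**What to change.** In Statistical Analyses, state that each habit-by-habit Spearman coefficient will be reported twice: pooled, and as a partial coefficient adjusted for division-by-status cell. The adjustment should centre ranks within cell or use indicator variables. The 1–4 and 1–3 codes cannot serve, because they impose an arbitrary order and a linear trend on unordered groups. Add that the pooled value describes the department, and that statements about how habits go together within people of the same group rest on the partial value.

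The cost is one or two sentences, a few lines of syntax and no new data. Four divisions by three statuses give at most 12 cells, so at most 12 − 1 = 11 degrees of freedom are used, out of up to 823 participants. The exploratory table gains one set of coefficients.

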## Results

This longitudinal study was started during the lockdown in Switzerland, in mid-April 2020 and will be completed in May 2021. The first phase of the study is underway, and data from 823 participants will be evaluated.

## Discussion

This paper outlines the study protocol of the survey conducted among BFH-DHP students and employees to evaluate their physical activity, nutritional habits, and sleep behavior during the 2020 COVID-19 confinement. This protocol has been developed as an interdisciplinary collaboration between faculty members of the Divisions of Nutrition and Dietetics and Physiotherapy.

During the same period, similar initiatives were undertaken by other institutes. For example, a large survey developed by a consortium of many international universities aimed to retrospectively evaluate the changes in lifestyle habits among the general population in context of the COVID-19 pandemic [2,15,16].

One of the strengths of our survey is that it will be short (time needed to complete the survey will be less than 10 minutes), limiting the questions to physical activity, nutritional habits, and sleep behavior within a specific setting of students and employees of BFH-DHP. We believe, this will help the participants place special focus on the current and future multipliers of healthy lifestyle habits and their own personal behavioral changes due to a general lockdown effected as a key countermeasure to combat the spread of the COVID-19 pandemic. Another strength of our survey is its prospective design over a 1-year period. Based on the large sample size comprising eligible staff and students (N>1500) and considering the huge impact of COVID-19–related strict measures on both the staff and students, we expect a reasonable response rate (ie, around 30%).
It may be hypothesized that such a confinement period may negatively affect physical activity levels of individuals, in general, and students and employees of BFH-DHP, in particular. In an effort to support the public in maintaining “healthy” physical activity levels, Swiss television channels resumed broadcasting home exercise programs after almost two decades. During this time, popular press reported an increase in the demand for fresh vegetables and fruit, as well as alcoholic beverages. Our survey will aim to verify and, if applicable, quantify such observations and put them in proper context.

The results of this survey may have important public health impacts. They may empower heads of universities and higher education institutions to better prepare, inform, and counsel their students and employees on maintaining healthy lifestyle habits that may prove useful, for example, in case of an upcoming second wave of COVID-19 or a sudden outbreak of a serious new viral epidemic or pandemic in the future. Action plans for workplace health promotions may be developed with a special focus on digital dissemination routes to reach students and employees in their home-office settings.

Several biases can occur in cohort studies, which should be reduced. For instance, a selection bias resulting from the approach used to select or observe study participants, which may influence the relationship between exposure and outcome. To avoid this type of bias, this study will recruit persons from only a single institution, ie, BFH-DHP. Second, an information bias could originate either from the individuals being observed, observers, or instruments used to evaluate the results. In prospective cohorts, information bias can usually be easily avoided since measures can be taken during scheduling by including all variables in the registration forms (instruments) so that no variables of interest are overlooked.

Nevertheless, this study has limitations. The survey does not collect any data about illnesses among participants during the first phase, which could likely influence a change in the targeted behaviors.

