**Methods:**

This paper describes a protocol for a retrospective and prospective observational cohort study. Students and employees of Bern University of Applied Sciences, Department of Health Professions, were invited to anonymously complete a web-based survey during the COVID-19 confinement period. This will be followed by a second survey, scheduled 1 year after the lockdown. Information on various lifestyle aspects, including physical activity, nutritional habits, and sleep behavior, will be collected using adaptations of existing validated questionnaires.

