#### Secondary Outcomes

##### Nutritional Habits

The valid German version of the Mediterranean diet screener (bMDSC) [13] will be used to assess the participants’ nutritional habits and adherence to the Mediterranean diet. Participants will be asked to report their adherence to the recommended consumption frequency of 15 selected food items during the past year: (1) use of olive oil for cooking; (2) use of olive oil as salad dressing; (3) daily intake of cooked vegetables; (4) daily intake of raw vegetables; (5) daily intake of fruits; (6) daily intake of red meat or sausages; (7) intake of butter and bread for breakfast or dinner; (8) intake of soft drinks or sweetened drinks on the previous day; (9) attention to nutritional fiber intake; (10) weekly intake of legumes, chickpeas, and beans; (11) intake of fish 1-2 times per week; (12) consumption of nuts at least at 3 days per week; (13) preference of white meat over read meat; (14) intake of rice or pasta with vegetable sauce as part of the diet; and (15) consumption of French fries on the previous day [14]. Response categories will be “Yes” or “No.” All questions will be scored “1” if answered with “Yes,” except questions (6), (7), (8), and (15) that will be scored “1” if answered as “No.” Scores will be summed, and a higher score will indicate better adherence to the Mediterranean diet.

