##### Alcohol Intake

Daily consumption of wine, beer, and spirits (liquor) will be evaluated and measured in units (glasses). For instance, how many units (glasses) of wine, beer, and spirits are consumed per day?

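### The survey is said to verify and quantify lockdown increases in vegetable, fruit and alcohol demand, but it has no pre-lockdown baseline or change question for them, and its diet items look back over a mostly pre-lockdown year

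*Protocol article*

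**What the plan says.** The Discussion reports that the "popular press reported an increase in the demand for fresh vegetables and fruit, as well as alcoholic beverages", and continues: "Our survey will aim to verify and, if applicable, quantify such observations and put them in proper context".

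The instruments for these intakes are described under Secondary Outcomes:

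- **Diet (Nutritional Habits).** "Participants will be asked to report their adherence to the recommended consumption frequency of 15 selected food items during the past year". The relevant items are cooked vegetables (item 3) and "4) daily intake of raw vegetables; (5) daily intake of fruits". On format: "Response categories will be “Yes” or “No".
- **Alcohol (Alcohol Intake).** "Daily consumption of wine, beer, and spirits (liquor) will be evaluated and measured in units (glasses", with the example question "how many units (glasses) of wine, beer, and spirits are consumed per day".

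The comparisons are described elsewhere. Second Survey and Data Collection plan the same questionnaire about a year later and a comparison of the confinement period with the period after it. Statistical Analyses plans a comparison with general-population values from before COVID-19. Study Setting states that the first survey took no personal or sociodemographic information.

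**The concern.** The press reports describe increases, and an increase during lockdown is a change from before lockdown. Verifying it needs either a measurement taken before confinement or a question asking respondents to compare the two periods. The article describes neither for vegetables, fruit or alcohol. Both survey waves come after 16 March 2020, and the only change question mentioned, on smoking in the second survey, concerns a different habit.

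The risk is one of interpretation. A 2020 level, a gap from an outside population, or a 2020-to-2021 difference could be read as confirming or refuting a lockdown increase that was not measured. The Discussion wants the results used to counsel students and staff in a future outbreak, so such a reading would have consequences.

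**Working it through.** The article gives no sample size, effect size or precision for this aim, so there is no figure of its own to reproduce. The check compares recall windows with dates and then looks at each available contrast.

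**Inputs**

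- Confinement began on 16 March 2020, and most measures were withdrawn on 11 May 2020 (Introduction).
- The first survey was open for one week and closed by the end of April 2020 (Data Collection). Results gives a mid-April start. The exact dates are not stated, so 15 to 30 April 2020 is assumed as the range.
- The second survey is in May 2021 (Study Setting). Any date from 1 to 31 May is allowed for.
- The diet recall window is the past year, taken as 365 days (Nutritional Habits).

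**1. Share of the first diet window that lies in confinement**

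Share = (survey date − 16 March 2020) / 365.

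| Survey date | Days in confinement | Share in confinement | Share before lockdown |
|---|---|---|---|
| 15 April 2020 | 30 | 30/365 = 8.2% | 91.8% |
| 30 April 2020 | 45 | 45/365 = 12.3% | 87.7% |

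**2. Dilution of a lockdown rise in a past-year average**

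If intake rose by a fraction r in confinement only, the past-year average rises by r × days/365. The values of r are illustrations, not figures from the article.

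| Assumed rise r | 30 days | 45 days |
|---|---|---|
| 20% | 0.20 × 30/365 = 1.6% | 0.20 × 45/365 = 2.5% |
| 50% | 0.50 × 30/365 = 4.1% | 0.50 × 45/365 = 6.2% |

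A Yes/No item then registers only respondents whose answer crosses the threshold. It carries no information on how much intake moved.

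**3. The second diet window**

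Overlap with confinement = 11 May 2020 − (survey date minus one year), not below zero.

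- Survey on 1 May 2021: the window opens on 1 May 2020, so the overlap is 10 days (10/365 = 2.7%).
- Survey on 11 May 2021 or later: 0 days.

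The 2020-to-2021 diet contrast therefore sets a year that is about 88% to 92% pre-lockdown against a year almost wholly after the lockdown. Neither window isolates confinement.

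**4. Alcohol**

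The item is a current quantity, so the recall-window problem does not arise. Two comparators are available:

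- The 2021 survey, which follows confinement and is not a pre-lockdown level.
- Pre-COVID-19 general-population values (Statistical Analyses). The eligible students are 88% female (Eligibility Criteria) and all respondents belong to a health-professions department. With no sociodemographic data in 2020, the first survey cannot be adjusted or standardised to that population. A difference from it is a difference in level between two groups, not a change within this one.

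**The case against.** The strongest reply has four parts.

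- **The plan does have a pre-COVID-19 comparator.** This stands: it would be wrong to say no pre-lockdown comparison is planned. It is an external comparison that cannot be standardised, so it does not yield a change in this cohort.
- **The items are not blind to increases.** A reader might infer that they can never show a rise. The article does not support that. Alcohol is a count and can be compared with 2021 or with outside values, and a Yes/No item does register people who move from No to Yes. The limits are the missing baseline and, for diet, the past-year window and the lack of any quantity.
- **The sentence is a hedged remark in the Discussion.** The objective in the Abstract is to evaluate habits during confinement and one year after, and the primary outcome is physical activity over the last 7 days. This stands and limits the weight of the point, although the Introduction and the Abstract's conclusions also speak of the impact of confinement.
- **The word retrospective promises nothing about change.** The Abstract says "This paper describes a protocol for a retrospective and prospective observational cohort study". A reader might take this as a commitment to ask about the time before lockdown. Past-year and 7-day recall are themselves retrospective, so the label does not show that a question is missing.

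It would also be too much to extend the point to sleep, which is not among the reported observations to be verified. Nor does the article say that a level or a 2020-to-2021 difference will be reported as proof of a lockdown increase. That is a risk left open by the wording.

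**Conclusion.** The point holds in limited form: the Discussion claims a capability that the described design lacks.

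- **Fruit and vegetables.** The items can neither isolate nor quantify a lockdown change. This rests on the stated past-year window and an assumed first-survey date of 15 to 30 April 2020. If respondents answered about their current habits instead, the answers would be closer to confinement but would still be Yes/No, with no earlier value.
- **Alcohol.** The item gives a level during confinement. An increase could be addressed only through a post-confinement comparison or an external one that cannot be standardised.

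The article gives no basis for stating the loss as zero precision or as a percentage of respondents unable to show a rise. The primary outcome is not affected. The correction is worth making because it is mainly wording and because, on the article's timeline, the second survey has not yet been run.

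**What to change.** 1. **Replace the Discussion sentence.** State that the survey does not verify or quantify lockdown increases in vegetable, fruit or alcohol intake, that the first survey's alcohol data describe levels during confinement, and that its diet score reflects the past year, most of which preceded confinement.
2. **Relabel the diet contrast.** Do not describe the 2020-to-2021 diet comparison as during versus after confinement. Describe it by its two recall windows.
3. **Restrict reference comparisons.** Compare with pre-COVID-19 values only where instrument, scoring and recall period match, and interpret the results as differences in level, not as change.
4. **Add recalled-change items to the second survey.** Use separate short items for alcohol, fruit and vegetables, asking about the spring 2020 lockdown compared with before (less / same / more). State the reference period in each item. Report them as recalled direction of change only. They give a comparison within each respondent without linking the anonymous waves.

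The cost is a few sentences of text and three short items. Recall over about one year is imprecise, so the new items can indicate direction but cannot quantify an increase.
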